### Statistical analysis

The aim of the main analysis is to compare the incidence, severity, and duration of delirium in pre- and post-HELP patient groups. To correct for the clustering of patients within wards and for baseline characteristics, multi-level analysis using the R statistical package will be used to evaluate differences in treatment outcomes between the two groups [40]. Estimates will be reported with 95% confidence intervals. The analysis will be conducted according to the intention-to-treat principle.

Missing data will be corrected using multiple imputation.

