### Study population

Eligible participants are patients ages 70 years and older who are at risk for delirium and are admitted to the cardiology, internal medicine, geriatrics, orthopedics and surgery units of the two hospitals. The Diakonessenhuis is situated in two locations (one in a university city and one in a smaller town nearby), while the Hospital Gelderse Vallei is located in a more rural area.

Eligible patients will be approached by the nurse on call for participation within 24-hours after hospital admission. Inclusion criteria are being 70 years and older, the absence of delirium at hospital admission and being considered at risk for delirium.

To assess whether a patient is at risk for delirium, we use the three questions of the Hospital Safety Program launched in the Netherlands in 2009 that are part of obligatory hospital care. A review of literature was done before choosing these questions [26]. The nurse will assess the risk for delirium in patients 70 years and older with the following questions: “Do you have memory problems?”; “During the past 24-hours, did you need assistance with your daily self-care?”; and “Were you confused during earlier hospital admissions or illnesses?”. When at least one of these questions is answered positively, there is an increased risk of delirium.

Exclusion criteria include a life threatening situation, being in a palliative phase at admission, an expected hospital stay of 24 hours or less, being legally incapable of participating, unable to communicate verbally, or a second hospital admission during the study period. If the patients are transferred to a participating unit, they are treated as a newly admitted patient; if the patients are transferred from a participating unit to a nonparticipating unit, they are excluded from the study.

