### Sample size

The sample size calculation was based on the primary endpoint incidence of delirium, as diagnosed by the Confusion Assessment Method (CAM) [27]. According to the literature, 10-40% of older hospitalized patients develop delirium [28-30]. HELP has been shown to reduce the absolute rate of delirium by 14.4%, which represented a relative risk reduction of 35.3% [17]. Thus, the difference in delirium incidence between the HELP-intervention group and the care-as-usual group was conservatively estimated to be at least 10%. To demonstrate this difference, using a two-sided test with an alpha of 0.05 and a power of 0.90, two groups of 470 patients are required, indicating a study population of 940 patients. Estimating that 15% of patients will not be willing to participate, the total number of patients to be included was estimated to be 1081 patients.

A total of 1648 patients ages 70 and older are hospitalized annually in the Diakonessenhuis. In the Hospital Gelderse Vallei, a total of 1393 patients aged 70 years and older are hospitalized annually. These hospitalizations result in 3,041 patients admitted per year, of whom at least two-thirds are expected to be at risk for delirium. This expectation is based on figures from hospitals that have already implemented the three question delirium risk assessment. This calculation should be sufficient for determining the total number of participants that are needed (n = 1,081) for the proposed study.

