### The implementation

Three months prior to the first hospital unit starting with HELP, all participating units will receive presentations on the content of the study and the measurements. The purpose of this period is to draw attention to the measurements that nursing should use to assess a patient’s risk for delirium. Baseline data will be collected during this time.

As described, every three months, one hospital unit in both hospitals will start the intervention. The four hospital units in both hospitals are comparable. The units that admit the most older patients were chosen. The staff will be made aware of the study’s time schedule and will know when they are in the control or intervention period. Before the unit starts with the intervention, a team of HELP volunteers will be assembled and will receive a two day training program that was specially developed for HELP. The researcher and local project leader will work closely with the volunteer coordinator, the trainers and the head of the hospital unit. The researcher will give regular presentations for the nurses of the hospital unit and will keep the hospitals informed with regular newsletters and messages on the hospitals’ webpages. The doctors, physical therapists and other professionals in the hospital unit will be informed by the project leader.

Each hospital has created a group of experts that gathers approximately every two months to discuss the HELP plans and its progress. This group can consist of the head and nurses of the participating hospital units, a doctor, the volunteer coordinator and the project leader.

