In the Netherlands, screening for delirium in older people has been a quality of care indicator of the Dutch Health Care Inspectorate (IGZ) since January 2010. As a result, hospitals are required to report delirium incidence and to develop policies on delirium prevention [26]. Our data collection closely aligns with this quality measure and strengthens the hospitals’ desire to participate. Given the stepped-wedge design and the fact that measurements are part of regular care, the Nurse Practitioners who are responsible for measuring the primary outcome know which patients receive the intervention. The lack of blinding is preempted by written protocols for screening, and diagnosis as well as the highly standardizes intervention. Moreover units are their own controls and at the same time their data can be compared to data of a comparable unit in the other hospital. To overcome the lack of blinding and ensure reliability of the primary outcome much emphasis will be given to training of the Nurse Practitioners. In addition, CAM interrater reliability between the Nurse Practitioners and between the Nurse Practitioner and a geriatrician will be tested regularly during the study. Finally delirium incidence can be compared with historical data of the participating wards using the procedure described by Rubin et al. in 2006.

Although delirium screening is part of regular care, the protocols are not always followed; this study may improve the percentage of screening for delirium. Thus, an increase in the number of patients with delirium risk is expected, most likely resulting in more delirium diagnoses. Three months prior to the start of the study, the researchers will pay close attention to the measurements that should be part of regular care to achieve the same starting point for all units. This coordinated effort will result in reliable baseline data on delirium risk and delirium diagnosis in all participating hospital units. If HELP proves to be effective, the chance of implementation of the protocol is largely due to the alignment of the aims with screening regulations and developments in health care standards.

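### The stated primary analysis contrasts pre- and post-HELP patients without adjusting for calendar time, so any drift in delirium incidence or detection enters the HELP estimate

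*Protocol article*

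**What the plan says.** The Statistical analysis section of the protocol article makes two statements about the main analysis. Its aim is to "compare the incidence, severity, and duration of delirium in pre- and post-HELP patient groups". Its model is described by what it corrects for: "To correct for the clustering of patients within wards and for baseline characteristics, multi-level analysis using the R statistical package will be used". No period, step or calendar-time term is mentioned there or elsewhere in the article.

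The design is a stepped wedge in eight units over 18 months. Under The implementation, one unit in each hospital starts HELP every three months, which makes four steps of two units. The Abstract says the order is random. A three-month preparation period comes before the first start, and of it the article says: "Baseline data will be collected during this time".

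The Discussion expects the study to improve adherence to screening, so that "an increase in the number of patients with delirium risk is expected, most likely resulting in more delirium diagnoses". Its answers are the lead-in, units serving as their own controls, a possible comparison with the matching unit in the other hospital, and a possible comparison with historical ward data.

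**The concern.** In a one-directional stepped wedge, exposure and time are tied together by design. A ward that is its own control is protected against fixed differences between wards but not against change over time: without a time term, the within-ward contrast is a before-after comparison. Randomising the order of the wards does not remove this from the estimate, because every ward moves the same way.

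The article states both the contrast and what the model corrects for, so this is more than a detail left for an analysis plan. Followed as written, the analysis assigns any drift to HELP. Rising detection would hide a real benefit, and falling incidence would exaggerate a benefit or create one. The Costs-evaluation section relates cost differences to differences in delirium cases, so the cost-effectiveness ratio would carry the same error.

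**Working it through.** **1. The plan's own sample size.** Inputs from Sample size: "using a two-sided test with an alpha of 0.05 and a power of 0.90", and a difference "conservatively estimated to be at least 10" percentage points. The control rate is not fixed; the article cites that "10-40% of older hospitalized patients develop delirium". The source effect (14.4 points absolute, 35.3% relative) implies 14.4/0.353 = 40.8% in controls, so I take 40% versus 30%.

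n per group = [1.96·√(2·0.35·0.65) + 1.282·√(0.40·0.60 + 0.30·0.70)]² / 0.10² = 477 (473 with unpooled variance).

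The stated 470 per group is reproduced and is not in dispute. It is, however, a figure for two independent groups, with no ward clustering and no time adjustment.

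**2. How much drift the estimate absorbs.** Take T periods and a ward with s control periods. Its mean control period is (s + 1)/2 and its mean HELP period is (s + 1 + T)/2. The difference is T/2, whatever s is. With ward fixed effects, a linear drift of d points per quarter therefore biases the HELP effect by d·T/2: 2.5d for five periods, 3.0d for six, 3.5d for seven.

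With a random ward intercept, as in a multi-level model, the multiplier is slightly smaller. I computed it by generalised least squares on ward-by-period means.

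**3. Assumptions.** The article gives no ICC or drift size, and its schedule table is in an additional file that is not shown. I assumed:
- five, six or seven three-month periods, with two wards starting at each of four steps;
- N = 940 in equal cells;
- average incidence 35%, so patient-level variance is 0.35·0.65 = 0.2275;
- ICC 0 to 0.05;
- a linear trend and normal-approximation tests.

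**4. Results.** Ranges run from ICC 0 to ICC 0.05.

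| Periods | Multiplier | Type I error, 0.5 point/quarter | 1 point/quarter | 2 points/quarter | Power for 10 points, no time term | Power with period effects | Variance ratio |
|---|---|---|---|---|---|---|---|
| 5 | 2.00–2.42 | 6.2–6.5% | 9.9–11.2% | 25–31% | 85–90% | 47–62% | 2.0–2.5 |
| 6 | 2.57–2.93 | 6.9–7.3% | 12.9–14.5% | 37–43% | 86–89% | 44–55% | 2.3–2.9 |
| 7 | 3.11–3.44 | 7.7–8.1% | 16.0–17.9% | 48–54% | 85–87% | 40–48% | 2.6–3.1 |

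With fixed period effects in the model, the bias is zero.

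**5. One row in full.** Six periods, ICC 0.02, 940/48 = 19.6 patients per cell. The multiplier is 2.86, and the standard error is 0.0329 without period effects and 0.0546 with them.
- Bias at 2 points per quarter: 2.86 × 2 = 5.7 points.
- Type I error: bias/SE = 0.0572/0.0329 = 1.74, and 1 − Φ(1.96 − 1.74) is about 41%.
- Power without a time term: Φ(0.10/0.0329 − 1.96) = Φ(1.08), about 86%.
- Power with period effects: Φ(0.10/0.0546 − 1.96) = Φ(−0.13), about 45%.
- Variance ratio: (0.0546/0.0329)² = 2.75.

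**The case against.** The strongest reply is that this is a short paragraph in a journal article. It explains why a multi-level model is used, gives no full formula and excludes no term, and an analysis plan that is not shown could add period effects. That stands as far as it goes: the article does not say that time is left out on purpose. But it does list what is corrected for, names the contrast as pre versus post, and omits the one confounder that the design creates.

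Four stronger readings are tempting, and the document does not support them.

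- **That the estimate is biased outright.** It is biased only if incidence or detection drifts after the lead-in. The size of any drift is unknown, and at 0.5 point per quarter the inflation of type I error is small.
- **That the Discussion predicts a continuing drift.** It mainly describes a rise from pre-study practice, which the lead-in is meant to absorb, and it speaks of numbers of at-risk patients and diagnoses, not of incidence among those enrolled. The lead-in is a sufficient answer only if detection is stable from then on, and the article does not show that it will be.
- **That other clauses show a trend.** Excluding "a second hospital admission during the study period" could deplete frail patients over time, and national prevention policy could lower incidence. The article gives neither a size nor a direction for either.
- **That random order protects only if period is modelled.** A permutation test over the start orders held type I error at 4.9% in a simulation with a 2-point drift and no period term. It does not correct the point estimate, and the article does not propose such a test.

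The comparisons with the other hospital's unit and with historical data are offered as possibilities and are not part of the stated model. Historical data would also add a further contrast in time.

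**Conclusion.** The point holds in conditional form. The stated adjustment set omits calendar time in a design where HELP patients are later than control patients within every ward. Any drift after the lead-in enters the HELP estimate at about 2.0 to 3.4 times its quarterly size. Drifts of 1 to 2 points per quarter would produce about 2 to 7 points of bias against a 10-point target; type I error would be about 10% to 18% at 1 point and 25% to 54% at 2 points.

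The multiplier follows from the design, given the assumed number of periods and ICC. The drift sizes are illustrations and not forecasts. Because the direction of any drift cannot be known in advance and this is the primary estimate, the model should be corrected before the data are analysed.

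**What to change.** Name the time term in the primary model: a mixed model for delirium with the HELP indicator, fixed effects for each three-month calendar period, a ward effect and the baseline covariates. Use the same time terms for severity, duration and costs.

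No new measurements are needed, but the change is more than wording. The confidence interval widens, with variance about two to three times as large. Power for a 10-point difference at N = 940 falls from about 85–90% without a time term to about 40–62% with period effects, under the assumptions above. The 90% power in Sample size should therefore be restated for the stepped-wedge analysis, with the ICC and number of periods given, and the target number reconsidered in that light.

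A small-sample correction or permutation test for the eight wards, ward-by-period effects, and a sensitivity analysis without the lead-in are optional additions.

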### Qualitative analyses

The aim of the qualitative research question is to incorporate viewpoints to be included in future HELP-training protocols and HELP-manuals for Dutch institutions that want to implement HELP. This information will enhance the chance of a successful implementation.

The qualitative study will use a grounded theory approach to analyze the experiences of patients and HELP-team members. Grounded research combines two data analysis processes; all data are coded and systematically analyzed to verify or prove a proposition [25]. The researcher does not necessarily engage in coding data but merely inspects the data for categories, makes memos and develops ideas [25]. Emerging themes during the process of data collection lead to implementation of these themes in following interviews. To examine the content of the interviews, an encoding scheme using a systematic and iterative method will be employed. The goal of this process is to elicit the meaning of an experience from the viewpoint of those who have had that experience. Data will be transcribed and analyzed using computer assisted qualitative data analysis software, Nvivo 9 (QSR International).

### Costs-evaluation

Differences in total mean costs between groups will be related to the differences in the number of cases of delirium and of the QALYs gained after three months. QALYs will be calculated by multiplying the utility of a health situation by the time spent in these health situations. The incremental cost effectiveness ratio (ICER) will be calculated and graphically presented as a scatter of bootstrapped ICERs on the cost-effectiveness plane and as an acceptability curve for a series of willingness to pay ceilings. Sensitivity analyses will be conducted that will focus on the most salient cost-drivers.

## Discussion

This is the first study to implement and study efficacy and cost-effectiveness of the Hospital Elder Life Program (HELP) in the Netherlands. HELP has proven (cost-)effective in the US and Canada, and for that reason, the project group decided to stay as close to the HELP protocols as possible when implementing HELP in the Dutch hospital care system. Necessary adjustments, including a more involved role for the nurses and specific delirium screening methods, were discussed with and approved by [name], the developer of HELP.

A controlled clinical trial with prospective, individual matching to compare patients admitted to one intervention and two usual-care (control) units was used in the original HELP study [13]. Randomization on the level of patients was not possible due to logistic reasons. This design demands comparable units, of which one can be prepared as an intervention unit and one as a control unit. However, in Dutch hospitals, only one unit per medical specialty is available. The stepped-wedge design is a specific cluster randomized controlled study design that is useful for the evaluation of patient safety interventions, such as HELP [41,42]. Moreover, the stepped-wedge design has statistical advantages. Hospital units act as their own control and hence provide data points for both the control and intervention units [41,42]. This feature of the stepped-wedge design reduces the risk of bias, which may be the most important issue in non-randomized studies. HELP will be implemented in two hospitals in two different cities, one of which is located in a rural area. The hospitals are similar in size, and the chosen units are comparable; these factors increase the generalizability of the results of this study to the Dutch hospital care system. The hospitals involved in this project are motivated to implement HELP and admit a relatively high number of older patients as a result of the demographics in their regions.

In the Netherlands, screening for delirium in older people has been a quality of care indicator of the Dutch Health Care Inspectorate (IGZ) since January 2010. As a result, hospitals are required to report delirium incidence and to develop policies on delirium prevention [26]. Our data collection closely aligns with this quality measure and strengthens the hospitals’ desire to participate. Given the stepped-wedge design and the fact that measurements are part of regular care, the Nurse Practitioners who are responsible for measuring the primary outcome know which patients receive the intervention. The lack of blinding is preempted by written protocols for screening, and diagnosis as well as the highly standardizes intervention. Moreover units are their own controls and at the same time their data can be compared to data of a comparable unit in the other hospital. To overcome the lack of blinding and ensure reliability of the primary outcome much emphasis will be given to training of the Nurse Practitioners. In addition, CAM interrater reliability between the Nurse Practitioners and between the Nurse Practitioner and a geriatrician will be tested regularly during the study. Finally delirium incidence can be compared with historical data of the participating wards using the procedure described by Rubin et al. in 2006.

Although delirium screening is part of regular care, the protocols are not always followed; this study may improve the percentage of screening for delirium. Thus, an increase in the number of patients with delirium risk is expected, most likely resulting in more delirium diagnoses. Three months prior to the start of the study, the researchers will pay close attention to the measurements that should be part of regular care to achieve the same starting point for all units. This coordinated effort will result in reliable baseline data on delirium risk and delirium diagnosis in all participating hospital units. If HELP proves to be effective, the chance of implementation of the protocol is largely due to the alignment of the aims with screening regulations and developments in health care standards.

Much attention will be paid to the recruitment, selection, training and coaching of volunteers. These individuals will receive a two day training and support from volunteer coordinators; a meeting will be organized every three months to allow the volunteers to share and evaluate their experiences. Before and after their activities, volunteers will also need to exchange information with nurses, which involves a change in the nurses’ work. The accessibility of the nurses will require attention from the project group.

A concern is the participation of an adequate number of older patients. The literature suggests that in older people, the refusal rate is higher than in younger populations. Several possible causes for this factor have been suggested. One reason described is that a lengthy and complicated patient letter with risks and benefits can be difficult to read and understand for frail older people [43]. The Medical Ethical Board considered this a low risk study; however, the Board has required that informed consent be obtained using a detailed and lengthy information letter, which may suggest that invasive research activities rather than additional care are being offered. It is therefore expected that fewer patients will be willing to sign consent.

HELP requires a fundamentally different view on the care organization and a change in the care process, including the introduction of methods of early recognition combined with care plans and the introduction of an Elderly Care Nurse Practitioner and trained volunteers to provide additional psychosocial support. Results of one cost-effectiveness study [17] showed that each patient who was prevented from becoming delirious saved the hospital $2,181. Although HELP has been implemented at a number of U.S., Canadian, Australian, and Taiwanese sites, only recently has the first implementation of a HELP-like program in a European hospital (Spain) been published [22]. The Dutch hospital care system and patient population are different than those of the USA. These differences have our utmost attention; in cooperation with the developers and users, we will try to implement HELP as closely as possible to the original protocols.

